#### Behavioural data analysis for neuroimaging measurement

Accuracy (%) and reaction times (ms [milliseconds]) will be recorded for the cognitive tasks [55] and additional signal detection indices will be calculated for the multi-object visual working memory task. Change in behavioural performance will be analysed for all three groups using a multilevel regression/repeated measures ANOVA, testing the task/group and by time interaction. Within this framework, group differences in change will be evaluated using contrast analyses.

##### EEG signals

For EEG signals associated with specific defined events, ERP data analysis will be conducted in Curry 8 (Compumedics, Charlotte, NC, USA). Raw continuous EEG will be re-referenced to linked mastoids and then bandpass filtered from 0.1 to 30 Hz. Eye blink artifacts will be corrected by electrooculography (EOG) regression method. Stimulus-locked epochs will be extracted from − 200 ms before to 1000 ms after the onsets of stimulus. Only trials with correct behavioural responses will be included in the subsequent ERP analyses. Epochs of the same experimental condition will be averaged to produce the ERP. The mean voltage between − 200 and 0 ms will be used for baseline correction. Electrodes chosen for analyses cover the two hemispheres and midline cortical regions. The six lateral electrodes that cover two hemispheres include Fp1 and Fp2 for prefrontal regions, F3 and F4 for the frontal regions, C3 and C4 for the central regions, T7 and T8 for the temporal regions, P3 and P4 for the parietal regions, and PO3 and PO4 for the parieto-occipital regions. The four electrodes that cover the midline regions are Fz, Cz, Pz, and POz. ERP components (P1, N1, N2 and P3), and their corresponding time windows will be identified from the grand averaged waveforms. The mean amplitude of each ERP component will be calculated for further statistical analysis.

##### MRI data analysis

The outcomes will be analysed at two points only (baseline and after 3 months). A time-series statistical analysis will be carried out using FILM (FMRIB S Improved Linear Model) with local autocorrelation correction [52]. To increase the power to detect group differences, to reduce the number of voxel-wise statistical comparisons, and to avoid risk of bias for subsequent analyses, the data from all subjects at both points of data collection (54 sessions) will be pooled to identify functional regions of interest (ROIs) for each task. Z-statistic images will be thresholded using a cluster correction method to account for multiple comparisons, as determined by Z42.3, to provide a brain-wise cluster significance threshold of p¼0.05.

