Using evidence-based rationale for patient flow in this study, we can assume that about 60% of patients screened will not be eligible for the study, due to age or lack of capacity to participate in the study [34]. Based on existing literature, we anticipate that about 45% of patients with schizophrenia will refuse to participate in the RCT studies [33], about 60% of patients screened will not be eligible for the study, and around 16% will drop out during the course of intervention [35]. Thus, we need a total of 1073 subjects to be approached and 237 participants to be randomly allocated to three study groups (79 patients/group) to ensure a final sample of 198 participants in the follow-ups (66 patients/group). These numbers are realistic given that the total number of patients with schizophrenia in our study sites is about 5500, and the total number of schizophrenia patients in Hong Kong is 40,000.

For the EEG analysis, a sub-sample of 50 patients in each group will be recruited (*N* = 150). For neuroimaging assessment using 3 T MRI and rs-fMRI, a sub-sample of 126 participants from our total sample (*N* = 198) will need (63%) to be randomised at baseline. Randomisation will be based on a list of computer-generated random numbers. We assume that 30% will drop-out between baseline and the 3-month follow-up assessment, which leaves us with 29 patients in each group (a total of 87 participants at baseline). The sample size will be appropriate for our neuroimaging assessment; the average number of participants in RCT studies assessing patient cognition [33] or changes in brain structure has been about 20 [14]. The flow-chart of the study is presented in Fig. 1.

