### Randomisation, allocation concealment and blinding (masking)

After baseline data collection, the trial manager will be notified of new participants. Each participant will be allocated to one of the three arms based on a list of computer-generated random numbers provided by an external clinical trial randomisation service (blocks of 6 consecutive patients, a 1:1:1 ratio). Allocation will be masked to the trial statistician, but it cannot be masked to the research assistants (RAs) who will supervise the gaming sessions and collect follow-up outcome data, or from the study unit staff who will work with the patients. Furthermore, a sub-sample of 150 participants will be recruited for EEG analysis, and 126 participants from our total sample will be randomly selected and assigned to neuroimaging assessment at baseline (fMRI). Again, the participants for neuroimaging assessment will be allocated based on a separate list of computer-generated random numbers provided by an external clinical trial randomisation service (blocks of 6 consecutive patients, a 1:1:1 ratio). The trial manager will inform the RAs the identities of participants allocated to fMRI assessment.

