##### Resting-state fMRI

In resting-state functional (rsfMRI) and structural MRIs, the most often reported neurocognition measurement for regions includes that of the nucleus accumbens, amygdala, striatum, anterior cingulate cortex, orbitofrontal cortex, and dorsolateral prefrontal cortex [50], the dorsal lateral prefrontal cortex and the anterior cingulate Testgyrus [51]. During the rsfMRI, the subject will not perform any tasks while being scanned. The rsfMRI is based on the principle that, even when the brain is at rest, there are still low fluctuations of neural activity. While the resting-state neural activity is at a much lower rate than when the brain is active, it can be used as a biomarker to study the underlying neuronal networks.

Comparing pre- and post-training records will reveal the impact of cognitive training with computerised exercises on the neuronal networks underlying the physiological basis of working memory ability. We will assess how the training influences inter-areal functional and structural (measured with MRI/Diffusion tensor imaging [DTI]) connectivity and the quantitative indices of cortical criticality and excitation/inhibition balance.

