**Study groups**							
Cognitive training with computerized exercises (experiment group)					X		
Entertainment video gaming (active control group)					X		
TAU (passive control group)							

^a^Convenience sample; ^b^Randomised subsample; ^c^ACP test planned but need to discontinue due to technological problems of the measure

First, for the primary and secondary outcomes (cognitive and social functioning, experience of pleasure, self-efficacy, negative symptoms), the data will be collected in paper format or digital format [5] by a trained psychologist or RA.

Second, the EEG will be recorded during resting state and a multi-objects visual working memory task (VWM). The task, modified from our prior studies [52], will be performed so that the neuronal mechanisms limiting VWM performance and capacity can be identified during the memory retention period. Subjects will attend either hemifield, depending on the pre-stimulus cue, and memorise a visual display containing one to six objects. After the retention period, a second stimulus will appear, and the subject will answer whether the stimulus presented in the second display matches part of the first display or not. We will correlate both local and large-scale neuronal dynamics with the task performance, both in pre-training and post-training neuroimaging sessions.

Third, fMRI scans will be acquired using a Philips 3 T MRI scanner. During scanning, a painless procedure, patients will rest on a table, which will be slid into a large tunnel-shaped scanner. As there will be a constant drumming noise during scanning, earplugs or earphones will be provided. During the examination, the patient will be able to freely communicate with staff via an intercom. Resting-state fMRI data will be acquired using T2-weighted echo planar pulse sequence imaging (300 whole-brain volumes were collected with slice thickness=4 mm, TE=30 ms, TR= 2000 ms, flip angle=90 degrees, spatial resolution 3x3x4 mm isotropic voxels, transverse orientation, 32 slices fully covering the cerebral cortex and the cerebellum, acquisition time = 10 min). Structural MRIs will be acquired with the MP-RAGE T1 sequence. A DTI of the axonal tracts in cerebral white matter will be performed with a protocol validated in the Human Connectome Project. We will acquire a 15-min session of resting-state data to obtain high-quality measurements of intrinsic functional connectivity of BOLD signals (fMRI) [53] and critical dynamics (fMRI) [54].

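### The MRI analysis derives task-based regions from 54 pooled sessions, but the trial scans at rest and its own MRI subsample implies 174 to 213 sessions

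*Protocol article*

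**What the plan says.** All references are to the protocol article.

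- **MRI data analysis.** Outcomes are analysed at baseline and 3 months. A time-series linear model (FILM) is fitted, and "the data from all subjects at both points of data collection (54 sessions) will be pooled to identify functional regions of interest". The regions are described as "functional regions of interest (ROIs) for each task". Z-statistic images are then thresholded with a cluster correction.
- **Resting-state fMRI.** "During the rsfMRI, the subject will not perform any tasks while being scanned". The section names functional and structural connectivity between areas, indices of cortical criticality, and excitation/inhibition balance as the quantities to assess. It also lists brain regions, introduced as those most often reported.
- **Data collection and follow-up.** The only fMRI acquisition is resting-state, alongside structural MRI and DTI. The multi-object visual working memory task is performed during the EEG. The resting-state run is given as 300 volumes at TR 2000 ms with a 10-minute acquisition time; the same paragraph later says "We will acquire a 15-min session of resting-state data".
- **Power analysis and sample size.** The plan takes "a sub-sample of 126 participants from our total sample", expressed as 63% of 198. It allows for a 30% loss before the second scan and gives the result in these words: "which leaves us with 29 patients in each group (a total of 87 participants at baseline".
- **Randomisation, allocation concealment and blinding.** "126 participants from our total sample will be randomly selected and assigned to neuroimaging assessment at baseline (fMRI", in a 1:1:1 ratio.
- **Data analysis, cognitive and clinical outcomes.** Outcomes measured at two time points, with the neurocognitive outcomes as the example, get a model with one time indicator and two group-by-time interaction terms.

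**The concern.** The MRI data analysis section conflicts with the rest of the article in two ways. It identifies regions by task, although nothing is performed in the scanner. It also gives a total session count far below what the planned subsample would produce.

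Imaging is a named secondary outcome and part of hypothesis 4, with two scans planned for up to 126 patients. The section presents pooling across subjects and visits as a safeguard against bias in later analyses. If that step cannot be carried out, the safeguard is lost, and the way fMRI measures are derived may end up being chosen once data are in hand. The surrounding figures (87 placed at baseline, 126 as a share of 198, two scan lengths) add to the uncertainty about what will be analysed.

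**Working it through.** **1. Reproduce the planned subsample.** Inputs: 126 participants, 1:1:1 allocation, 30% dropout by 3 months.

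- Per arm at baseline: 126 / 3 = 42.
- Per arm after dropout: 42 × (1 − 0.30) = 29.4, rounded down to 29.
- Total after dropout: 29 × 3 = 87.

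The plan's 29 per group and 87 in total reproduce, but as the number remaining at 3 months. Baseline is 126.

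**2. Try to reproduce 54 sessions.** Sessions = baseline scans + 3-month scans.

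| Reading | Sessions | 54 as a share |
|---|---|---|
| Completers only, 87 × 2 | 174 | 31% |
| All scans acquired, 126 + 87 | 213 | 25% |
| No dropout, 126 × 2 | 252 | 21% |
| 87 taken literally as baseline, 30% then lost, 87 + 61 | 148 | 36% |
| The same, completers only, 2 × 87 × 0.7 | about 122 | 44% |

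No reading gives 54.

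**3. Work backwards from 54.** With two scans each, 54 / 2 = 27 people, or 27 / 3 = 9 per arm. If 30% were lost after baseline, n × (1 + 0.7) = 54 gives n of about 32. Neither 27 nor 32 appears in the article as an imaging sample.

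**4. Check for a task.** The Resting-state fMRI section rules out a task in the scanner, and Data collection and follow-up schedules none. A section on behavioural data for neuroimaging refers to cognitive tasks, but the multi-object task it names is the one recorded with EEG. There is thus no in-scanner task from which to define regions.

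**5. Check the link from measure to test.** Connectivity is named as a quantity of interest, and a group-by-time model exists for neurocognitive outcomes. The MRI data analysis section mentions neither connectivity nor DTI, and no resting-state variable is named as the outcome of that model.

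**6. Related figures.**

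- 126 / 198 = 63.6%, the stated 63%. But 198 is the final follow-up sample, while the 126 are selected at baseline.
- The randomised total is 237 in Power analysis and sample size, but 234 in the Abstract and in Interventions (3 × 78). So 126 / 237 = 53.2% and 126 / 234 = 53.8%.
- 300 volumes × 2 s = 600 s = 10 minutes, which agrees with the stated acquisition time but not with the 15-minute session.

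**The case against.** The strongest reply is that the pooled step only identifies regions and is not the test of treatment effect. That test is given elsewhere, as group-by-time interactions for two-visit outcomes, and the quantities of interest are named in the Resting-state fMRI section. A time-series linear model, pooling over visits and cluster thresholding do not in themselves require a task; only the task wording does. This is also a condensed article, so details of the resting-state pipeline may properly sit in a fuller document.

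Much of this stands, and it limits the point. A reader might infer that hypothesis 4 cannot be tested on fMRI at all. The documents do not support that: the contrasts are specified, and the EEG and structural parts do not rely on this step. A reader might also infer that the paragraph was written for another study. The mismatch is compatible with that, but the article shows only that the paragraph does not fit this trial.

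Two further inferences fail. The 10- and 15-minute figures do not show that scan length will vary between sessions or patients, since a session may include more than the 300-volume run. Nor are the listed regions already this trial's prespecified ones; they are presented as commonly reported.

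The reply does not remove the contradictions. The session count and the task-based regions are stated, not omitted, and a fuller document would not make them agree with the design described here.

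**Conclusion.** The point holds in a limited form. The stated region-of-interest step contradicts the resting-state design and cannot be run as written. The 54 sessions are 31% of the 174 implied by completers and 25% of the 213 implied by all scans acquired; even the lowest reading gives about 122. These counts assume the plan's own 126 at baseline, 30% dropout and one imaging session per visit. In addition, no resting-state measure is connected to the two-visit model.

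The reach is confined to the fMRI component of an additional secondary outcome in a subsample. The primary outcome, the main randomisation and the main sample size calculation are untouched. It should be corrected before analysis because the contradiction is clear and the correction is cheap.

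**What to change.** Before analysis:

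1. In MRI data analysis, delete the reference to tasks. Replace the 54 with the count implied by the planned subsample: 174 if only completers are pooled, 213 if all acquired scans are.
2. Replace the task-based region step with resting-state measures of the connectivity quantities already named under Resting-state fMRI, using regions fixed in advance (for example, those listed there). Test these measures with the existing two-visit group-by-time interactions, with a stated multiplicity correction. Keep the structural MRI and DTI outcomes.
3. In Power analysis and sample size, label 87 as the 3-month number. Reconcile 234 with 237, then give 126 as 53.8% or 53.2% of the randomised total, not as a share of the 198 at follow-up.
4. In Data collection and follow-up, reconcile the 10-minute acquisition with the 15-minute resting-state session.

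The cost is one rewritten paragraph and a few corrected figures. No new scans are needed. The article reports recruitment as ongoing, so at that stage the change could still precede analysis.

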### Ethical issues

The WMA Declaration of Helsinki [56] and its ethical principles for medical research involving human subjects has guided our study design and protocol. The data collection will be voluntary based; written informed consent forms will be signed by patients. Prior to enrolment, participants will be made aware of all potential risks and benefits of participation (oral and written information). All steps will be taken to avoid any harm to participants. First, to minimise extra burden due to gaming interventions, playing intensity will be set at a maximum of 5 h per week, or it will be tailored to participants’ individual needs. Second, we have chosen video games that are purely fictional and do not include intentional violence. Third, possible changes in a patient’s health status will be continually monitored throughout the project. Fourth, players in this study will play the game under supervision only. Fifth, patients’ participation may be biased toward those who are interested in gaming, which will be taken into account in the conclusions. Any extra costs to the patients as a result of participation (treatment or travel costs, gaming licenses) will be covered.

## Discussion

This study will be the first clinical trial in Hong Kong to test the effectiveness of video gaming on improving cognitive and neurocognitive functioning in people with schizophrenia. The study will offer new insights into, and characterization of, the impact of using video gaming on patients’ health and well-being. The study will also contribute towards the development of new approaches to patient care in mental health services in Hong Kong. The results may also have implications for other health conditions in which motivational problems are related to health outcomes. The topic of the study is justified by the need to develop more innovative and engaging interventions for patients with schizophrenia [13]. However, before making recommendations for patients and especially decision makers, we should have an understanding of what the clinical outcomes of gaming interventions on health and well-being are. If ICT (Information and communications technology)-based interventions are to be taken as part of routine care without a clear understanding of how they work, there is the danger of using new interventions that may be non-effective and costly. If successful, the findings of this study will have the potential for remarkable societal and clinical impact, particularly in relation to changing treatment approaches and cultures in psychiatric services. In the long run, the findings could inform whether the gaming intervention could potentially reduce service costs and if our interventions are effective. It might also be possible that the study could result in a paradigm shift for non-medicinal treatment for schizophrenia, as this type of treatment is low-cost, easy to use and effective for cognitive symptoms of schizophrenia.

## Study status

Patient recruitment is ongoing.

## Data Availability

Not applicable.

## Abbreviations

AIMS: Abnormal Movement Involuntary Scale
BARS: Barnes Akathisia Rating Scale
BSPS: Brief Social Phobia Scale
CAINS: Clinical Assessment Interview for Negative Symptoms
CDS-C: Calgary Depression Scale for Schizophrenia
DSM-IV: Diagnostic and Statistical Manual of Mental Disorders, fifth edition
EEG: Electroencephalography
ECT: Electroconvulsive therapy
EOG: Electrooculography
ERP: Event-related potential
ES: Effect size
FILM: FMRIB S Improved Linear Model
fMRI: Functional magnetic resonance imaging
GSE: General Self-Efficacy Scale
ICT: Information and communications technology
IQ: Intelligence Quotient
LNST: Letter-Number-Span-Test
LOCF: Last observation carried forward
MANOVA: Multivariate analysis of variance
MMSE: Mini Mental State Examination
MRI: Magnetic Resonance Imaging
ms: Millisecond
NGO: Non-governmental organization
NIMH-MATRICS: US National of Institute of Mental Health, the Measurement and Treatment Research to Improve Cognition in Schizophrenia
RA: Research Assistant
RCT: Randomised controlled trial
ROIs: Regions of interest
SAS: Simpson-Angus Rating Scale
SPSS: Statistical Package for the Social Sciences
TEPS: Temporal Experience of Pleasure Scale
TMT: Trail Making Test
WMS: Wechsler Memory Scale
